#### Relevant concomitant care permitted or prohibited during the trial {11d}

There are no restrictions placed upon participants for any other professional activity during the trial.

### Provisions for post-trial care {30}

As an educational activity, there are no provisions made for post-trial care, nor any participant harms expected.

### Outcomes {12}

#### Outcome measures

##### Primary outcome measure

Difference in change in cost per 100 consultations of specified prescriptions, pathology and radiology test ordering in the intervention versus control groups for 6 months following the intervention compared with 6 months prior to the intervention.

Secondary outcome measures include the following:
Difference in change in rate per 100 consultations of specified prescriptions in the intervention versus control groups for 6 months following the intervention compared with 6 months prior to the intervention.Difference in change in rate per 100 consultations of specified pathology test ordering in the intervention versus control groups for 6 months following the intervention compared with 6 months prior to the intervention.Difference in change in rate per 100 consultations of specified radiology test ordering in the intervention versus control groups for 6 months following the intervention compared with 6 months prior to the intervention.Difference in change in knowledge assessment test results in the intervention versus control groups, for tests conducted prior to the intervention compared with following the intervention.

To assess GPs’ clinical decision-making in the context of the MHR clinical system, the trial will include semi-structured interviews with approximately 30 participants before and after the intervention (approximately 10 in each arm), the final number depending on the sample at which data saturation has been reached.

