### Objectives {7}

The objective of the study is to evaluate the effectiveness of a multifaceted educational intervention for Australian GPs. The educational intervention will be conducted by Medcast Pty Ltd. and is designed to support best-practice for prescribing, pathology and diagnostic imaging ordering in the context of the MHR system.

The trial will test the following primary hypothesis:
The education intervention will result in a reduction in the cost per 100 consultations of specified prescriptions, pathology and radiology test ordering in the intervention versus control groups in the 6 months following the intervention compared with 6 months prior to the intervention.

Secondary hypotheses include that the intervention will result in the following:
A reduction in the rate per 100 consultations of specified prescriptions in the intervention versus control groups in the 6 months prior to the intervention compared with 6 months following the interventionA reduction in the rate per 100 consultations of specified pathology test ordering in intervention versus control groups in the 6 months prior to the intervention compared with 6 months following the interventionA reduction in the rate per 100 consultations of specified radiology test ordering in the intervention versus control groups in 6 months prior to the intervention compared with 6 months following the interventionAn improvement in knowledge assessment test scores in the intervention versus control groups in tests conducted prior to the intervention compared with following the intervention.

The specified prescriptions, pathology and radiology items are listed in Table 1.

**Table 1 Tab1:** Target choosing wisely drugs and tests to inform the development of educational materials

List of choosing wisely based items	

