### Trial design {8}

The design is a pragmatic cluster-randomised three-arm parallel trial and a prospective qualitative inquiry. The effect of the education topic intervention in each arm will be assessed, using the other two arms as controls. A schematic diagram of the study design is presented in Fig. 1.

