### Interventions

#### Explanation for the choice of comparators {6b}

Trial participants will be randomised to one of three parallel arms. Each arm will receive different topic content for prescribing, pathology ordering or imaging ordering as a standardised education process intervention. Each arm will act as controls for each other, for example, participants in the pathology arm will act as controls for the imaging and prescribing arms; participants in the imaging arm will act as controls for the pathology and prescribing arms; and participants in the prescribing arm will act as controls for the imaging and pathology arms. In this manner, the change in clinician behaviour associated with the education intervention for a given topic content arm can be compared against clinicians receiving the equivalent education process exposure but for different topic content in the other two arms.

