##### Intervention

Medcast Pty Ltd. will develop and implement the education intervention which will focus on three topic streams running in parallel. The topic streams include a rational prescribing education intervention, a rational pathology-ordering education intervention and a rational diagnostic-imaging education intervention. All three topic streams will be in the context of the use of MHR in achieving quality improvement (QI) benefits and in integrating MHR into clinical practice. The ‘Choosing Wisely’ recommendations [5], an initiative of the National Prescribing Service Australia, will inform the education content, along with other sources of current evidence-based practice [6–11]. The Choosing Wisely recommendations, which are evidence-based, are supplied and endorsed by every peak medical and nursing body in Australia. The prescriptions and tests included in the study are specified a priori for the education sessions and then assessment. These same tests and prescriptions are assessed across all three arms of the trial 6 months pre- and post-intervention. The intervention pathology tests, imaging tests and prescription medication were chosen based on their frequency in general practice, cost to the PBS and potential for adverse outcomes in patients [13, 15, 16, 37].

Each GP participant will be required to complete pre- and post-intervention assessments for all of the prescribing, pathology and imaging educational domains, as although participants are randomised into one arm of the trial, the other two arms act as controls. This will allow assessment of the knowledge and skills acquisition of the GP participants, attributable to the arm of the intervention they have been randomised into, in comparison with the other arms. See Fig. 2 for a comparison of the educational activities in each arm.

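### The primary cost outcome pools three domains although every arm is taught, so as worded its contrasts rank topics against each other instead of showing the effect of the education on cost

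*Protocol article*

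**What the plan says.** Outcomes {12} gives the primary measure as "Difference in change in cost per 100 consultations of specified prescriptions, pathology and radiology test ordering in the intervention versus control groups", comparing the 6 months after with the 6 months before the intervention. The primary hypothesis in Objectives {7} has the same combined form: "The education intervention will result in a reduction in the cost per 100 consultations of specified prescriptions, pathology and radiology test ordering". The abstract repeats it.

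The secondary rate outcomes are split into three separate measures, for example "Difference in change in rate per 100 consultations of specified pathology test ordering in the intervention versus control groups". Sample size {14} calls single-domain analyses sub-group analyses.

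On the arms, section {6b} says: "Each arm will receive different topic content for prescribing, pathology ordering or imaging ordering as a standardised education process intervention". There is no untaught arm. Control is defined in Trial design {8}: "The effect of the education topic intervention in each arm will be assessed, using the other two arms as controls". Section {6b} adds "Each arm will act as controls for each other" and gives the rationale that GPs taught a topic are compared with "clinicians receiving the equivalent education process exposure but for different topic content in the other two arms". The Intervention section confirms that all items are measured everywhere: "These same tests and prescriptions are assessed across all three arms of the trial 6 months pre- and post-intervention".

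No section says which arm counts as intervention for the combined cost, or limits the cost to the arm's own domain.

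**The concern.** The comparator logic is topic-matched: an arm is a control for a domain because it was not taught that domain. A cost that adds the three domains removes that property. On total cost no arm is untaught, and each arm's saving is set against the savings of the other two.

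The primary hypothesis is that the education reduces cost. If the outcome is analysed as worded, an effective stream can come out as neutral or as raising cost, and the primary result would then be read as evidence against education that worked. The sponsor wants the trial to inform decisions about tangible economic benefit, so the error would fall on the result that matters most.

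**Working it through.** **The plan's own figure.** Sample size {14} states f2 = 0.15, 80% power, alpha 0.05 and 55 participants in two arms. With one tested predictor, the noncentral F test with lambda = 0.15 x 55 = 8.25 gives power 0.805, so the figure reproduces. The design effect is 1 + (3 - 1) x 0.05 = 1.10; 27.5 x 1.10 = 30.25, rounded up to 31 per arm, and 3 x 31 = 93. This calculation is framed for single-domain analyses and does not address a contrast on combined cost.

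**The combined-cost contrasts.** Let a, b and c be the true reductions in total cost produced by the prescribing, pathology and imaging arms. Comparing each arm with the mean of the other two (equal arms, as the 1:1:1 allocation intends) gives:

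- prescribing: -a + (b + c)/2
- pathology: -b + (a + c)/2
- imaging: -c + (a + b)/2

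The sum is -(a + b + c) + (a + b + c) = 0 for any a, b and c. The average saving therefore drops out. Unless all three contrasts are zero, at least one must be positive.

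**Size.** The documents give no cost shares, so they are assumed here. Each topic is also assumed to change only its own domain. A reduction of 15% lies within all three ranges quoted in the protocol's Education interventions section (prescriptions 15-20%, imaging 10-25%, pathology 10-20%). Those ranges are taken to carry over to cost. An arm's effect on total cost is minus its share times its on-topic reduction. Order throughout: prescribing, pathology, imaging.

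| Assumed shares (%) | Assumed on-topic reduction | True arm effects (% of total cost) | Combined-cost contrasts (%) |
|---|---|---|---|
| equal | 15% each | -5, -5, -5 | 0, 0, 0 |
| 50/30/20 | 15% each | -7.5, -4.5, -3.0 | -3.75, +0.75, +3.0 |
| 60/30/10 | 15% each | -9.0, -4.5, -1.5 | -6.0, +0.75, +5.25 |
| 80/15/5 | 15% each | -12, -2.25, -0.75 | -10.5, +4.1, +6.4 |
| equal | 15%, 10%, 10% | -5.0, -3.3, -3.3 | -1.7, +0.8, +0.8 |

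For 60/30/10 the steps are: -9.0 + (4.5 + 1.5)/2 = -6.0; -4.5 + (9.0 + 1.5)/2 = +0.75; -1.5 + (9.0 + 4.5)/2 = +5.25. In every row all three streams save money, yet at least one appears neutral or cost-raising.

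**The topic-matched alternative.** Take only the domain that the arm was taught. Under the same no-spillover assumption that domain's cost changes by -a, -b or -c in the taught arm and by 0 in the other two. The contrast is then -a, -b or -c, which is the full effect of the topic.

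**The case against.** The strongest reply is that the protocol already intends a topic-matched comparison. Trial design {8} and section {6b} define control only by topic. The rationale in {6a} expects reductions among GPs who received the relevant education. The secondary outcomes use the same intervention-versus-control phrase, and there it can only mean the taught arm against the other two. Section {20a} speaks of analysing each data element. This stands as evidence of a workable intention, and on that reading the trial does answer its hypothesis. It does not settle the wording: the secondary outcomes are split by domain, the primary is not, and the sub-group label in {14} favours a combined primary.

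A reader might go further and infer that the contrasts always cancel, or that the design cannot show a cost reduction at all. The documents do not support that. A sum of zero does not make each contrast zero; all three vanish only when absolute savings are equal across arms. Every domain is measured in every arm, so topic-specific cost effects can be estimated.

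A reader might also infer that error is uncontrolled if the primary is read as three domain tests. An adjustment or success rule may be in the analysis plan, which is not shown, so its absence here is not an error.

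It is also fair to say that the percentages depend on assumed cost shares. The zero sum does not.

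**Conclusion.** The concern holds as a badly fixed primary outcome, not as a failed design. Taken literally, the combined-cost contrasts sum to zero and carry information only on how topics differ from each other. The zero sum is algebraic for equally weighted arms. The sizes shown, such as -6.0%, +0.75% and +5.25% of total cost, rest on assumed shares, a 15% on-topic saving in each arm and no spillover between domains. This goes beyond missing detail, because following the stated outcome as written would give a misleading primary result and conflicts with the trial's own comparator rationale.

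**What to change.** Restate the primary outcome and hypothesis as the difference in change in on-topic cost per 100 consultations: prescribing cost for the prescribing arm, pathology cost for the pathology arm and imaging cost for the imaging arm, each against the other two arms. State how the three contrasts together answer the single primary hypothesis, for instance through one common on-topic effect, a fixed order or an adjusted set of tests; if the analysis plan already does this, refer to it. Report combined cost descriptively.

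No new data are needed. The price is three contrasts instead of one. With the protocol's f2 = 0.15 (d = 2 x sqrt(0.15) = 0.775) and design effect 1.10, the standard error for 31 versus 62 GPs is sqrt(1.1/31 + 1.1/62) = 0.231. By the normal approximation, power at two-sided 0.05 is about 92% per contrast. It is about 91% for 30 versus 60, which is what 40 per arm leaves after 25% attrition. Both figures assume that the effect planned for single-domain analyses such as prescribing rates carries over to cost.

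Section {25} requires ethics approval for outcome changes, and Trial status reports the trial as completed. The change should therefore be dated and disclosed, stating whether it came before or after access to outcome data.

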#### Economic impact

Economic evaluation of the educational intervention will consider the joint cost and effects of strategies aimed at reducing potentially inappropriate prescribing, pathology and imaging, and report on intervention costs per session and individuals trained. Quantitative practice change evidence from GP data audit pre-post-intervention will be triangulated with GP self-reported assessment of the impact of training by Medcast. Within the study, a cost-effectiveness analysis will focus on observed intervention cost and cost offsets and, where appropriate, net incremental cost per reduction in reduced use of potentially inappropriate medicines, pathology and imaging.

### Participant timeline {13}

The time schedule of enrolment in the trial, data collection and intervention activities is shown in Table 3 below.

**Table 3 Tab3:** CHIME-GP trial timeline

Task name	Start	Finish
**Participant recruitment**	**January 10, 2020**	**August 31, 2020**
o Invitations to participate will be communicated in recruitment waves via Medcast, PenCS, ADHA and UOW. Invitations will contain the study participant information sheet and consent forms for participants and practices as well as contact details of the research team.		
o Participants and practices expressing interest will send consent forms to the project officer at the University of Wollongong to be enrolled in the trial.		
**Participant randomisation**	**January 10, 2020**	**August 31, 2020**
o Randomisation of participants will occur after consent has been gained by participants and their practices. Each enrolled participant will be randomised into one of the three arms of the trial.		
**Data collection pre-intervention**	**January 10, 2020**	**September 10, 2020**
o A sample of consenting participants will be contacted directly by the research team to arrange qualitative interviews following randomisation. o GPs n = 30, 10 in each arm, approximately 30 min per interview		
o Pre-trial participant quizzes and case scenario activities will be collected by Medcast June–September 2020		
**Intervention period**	**June 2020**	**November 2020**
o Wave 1 webinars and online education modules June–August 2020		
o Wave 2 webinars and online education modules September–November 2020		
**Data collection post-intervention**	**September 1, 2020**	**May 31, 2021**
o The sample of consenting participants will be contacted directly by the research team to arrange follow-up qualitative interviews. o GPs *n* = 30, 10 in each arm, approximately 30 min per interview		
o Post-trial participant quizzes and case scenario activities will be collected by Medcast		
**Data extraction**	**June 1, 2021**	**June 1, 2021**
o Electronic Health Record data extraction for period November 2019–May 2021 o GPs n=40 in each arm, automated de-identified data extraction for 6 months prior to 6 months post-intervention		

### Sample size {14}

#### Sample size for quantitative data

The study is conservatively powered for testing significance in sub-group analyses (e.g. change in prescribing rates or change in pathology test ordering) with a 1:1 intervention: control allocation. As this is a three-arm trial, the final number of control cases in sub-group analyses will be twice those assumed in these calculations. A medium intervention effect (f2 = 0.15) is detectable at 80% power and α = 0.05 with 55 participants, in a two-arm trial (27.5 in each arm), analysed using a linear mixed model. The generally accepted practice level intra-cluster correlation coefficient (ICC) of GP behaviour is 0.05, and an average of three participating GPs per practice will be assumed. This results in a conservatively estimated design effect of 1.1. Thus, the target recruitment is a minimum of 31 participants in each of the three arms of the trial (n=93). To allow for 25% attrition, the study will aim to recruit 40 participants in each of the three arms (n=120).

#### Sample selection for qualitative data

On the consent form, GP participants will be asked to indicate whether they agree to be contacted for pre- and post-intervention interviews. A member of the research team invites participants, by their preferred contact method, to take part in 30 min pre- and post-interviews. The research team will use a purposive sampling approach (maximum diversity sampling) to derive the qualitative study sample, which will take into consideration participant age, sex, clinic size and location.

### Recruitment {15}

Medcast Pty Ltd., PenCS (a health analytics company providing data extraction services for the project), ADHA and the University of Wollongong (UOW) will send invitations to GPs in their pre-existing networks, and other known GP groups, inviting GPs from practices that already have PenCS software installed on their practice computing systems to participate (see also eligibility criteria section 10). The organisations sending out invitations will not have access to any of the email databases except their own.

The invitations will be sent to GPs and their practices, via email or other electronic media, with two follow-up reminders. If insufficient responses are received after sending two reminders, further invitations to new samples of GPs and practices will be sent in the above fashion (refer also to section 26A). Due to the 2020 global pandemic, COVID-19 [38], and its impact on recruitment into the study, we have extended the recruitment period to 8 months instead of the initial plan of 4 months, to enable the study to meet the recruitment target. In addition, two further reminder emails will be sent to all GP contacts until the recruitment target is met.

The invitations will have the Participant Information Sheets and Consent Forms attached. Interested GPs and their practices can respond by faxing or emailing consent forms to the UOW research team. Individual GPs as well as the responsible officer for practices will be required to complete consent forms (see also Section 27). Although consent will be obtained at the practice level and the individual GP level, only data relating to the consenting GPs will be extracted from the clinical information system in each practice.

### Assignment of interventions: allocation

#### Sequence generation {16a}

A stratified randomisation approach will be used to ensure a balance of practice sizes (≤ 5 GPs vs ≥ 6 GPs) and rurality. Randomisation will be conducted using the RALLOC command in STATA V15 or higher (StataCorp LLC., College Station Tx). While the study will be analysed at the level of individual participants, in order to minimise contamination of control groups, the education intervention will be randomised at a practice level.

#### Concealment mechanism {16b}

Randomisation will be carried out by the research team’s statisticians to one of the 3 groups. The statisticians will remain blinded as to the education intervention assigned to each group for analysis. The study participants will not be blinded as to allocation.

#### Implementation {16c}

After receipt of consent forms from practices and their associated GPs, a de-identified list will be compiled of practices and GPs including practice size (≤ 5 GPs vs ≥ 6 GPs) remoteness area of the practice (major city or other) [39] and number of GPs from the practices participating. No other information regarding the identity of the practice will be supplied. The statisticians ([name] and [name]) will apply a computerised stratified randomisation algorithm RALLOC (using STATA) to ensure a balanced allocation across each of the three arms of the trial according to practice size and remoteness area and number of participating GPs. GP participants and their practices will be randomised to one of the three topic streams (intervention arms) on a 1:1:1 basis. The statisticians will provide the project officer the randomisation sequence who will allocate the practices into the three trial arms on a first-come-first-serve basis. As outlined in the data management sections of the protocol, the statisticians will not have to access the coding sheets until after the final analysis is completed.

### Assignment of interventions: blinding

#### Who will be blinded {17a}

The statisticians will be blinded as to the intervention allocation for analysis. Trial participants, educators and other research team members will not be blinded.

#### Procedure for unblinding if needed {17b}

As no clinical treatments will be undertaken, the researchers do not believe there is a situation in which breaking the study codes will be required.

### Data collection and management

#### Plans for assessment and collection of outcomes {18a}

##### Quantitative data collection

PenCS will create an automatic data extraction macro that will extract relevant de-identified clinical data from the Electronic Health Records (EHRs) of the participating GPs at their participating practices. The de-identified clinical data will be encrypted and securely transferred directly from the GP practice server to a secure UOW data repository. Test quiz data will be collected by Medcast Pty Ltd. as part of the education intervention. These data will be securely transferred to the UOW data repository.

